#### Pilot Trial Design

Primary data collection for the pilot has entailed brief provider surveys and semistructured provider interviews drawing upon the CFIR to assess factors (barriers and facilitators) for pilot tool implementation. In addition, we intend to use the provider interviews and program reporting on pilot enrollment and service delivery to evaluate pilot implementation outcomes, drawing upon RE-AIM measures: reach (types and numbers of patients enrolled), effectiveness (preliminary effects on LAI ART uptake and concordance between treatment plan pursued and patient choice as recorded on the decision aid), adoption (documentation of specific tools’ use), implementation (alignment of reported tool use with study condition and guidance on tool use), and maintenance (ART adherence). This pilot study was designed as a nonrandomized, 2-arm trial of newly developed tools with ≥180 RWPA MCM patients. It was structured to allow comparison of an intervention arm including both patient education materials and the decision aid (*decision-aid arm*) with an intervention arm including only the patient education materials and usual care approaches (whatever agencies may already be doing) for ART regimen decision-making (*education-only arm*).

#### Study Setting and Participants

The pilot test was conducted at the 6 partnering RWPA MCM agencies. The characteristics and study arm assignments of the 6 agencies are summarized in Multimedia Appendix 1. Cluster (agency-level) assignment was used for this study to minimize crossover between intervention conditions and avert the logistical and ethical dilemmas posed by assignment strategies that require providers to administer, maintain, and track different investigator-assigned intervention conditions within a single patient caseload [54-56]. *Provider eligibility:* Pilot-related primary data collection was limited to English-speaking adults responsible for overseeing or delivering RWPA MCM services or prescribing ART for MCM patients at a partnering agency. At each agency, 1 administrative staff member (eg, program director) and 1 direct-service provider (eg, case manager, patient navigator, or prescriber) was engaged to participate in implementation-related data collection through brief surveys and semistructured interviews. *Patient eligibility:* Patients were enrolled in a partnering NY RWPA MCM program, aged ≥18 years, and able to understand materials in English or Spanish. Patient eligibility for an LAI ART prescription could not be directly assessed by the study team and could be assessed differently by different providers or third-party payers; it could also change over time with FDA label indications. However, the study team communicated to partnering programs that patients should not be included in the pilot if they had known or suspected resistance to cabotegravir or rilpivirine, as this was a contraindication for LAI ART available as of the start of this pilot study (CABENUVA). On the basis of AB feedback that translating pilot materials to Spanish without translating to Haitian Creole would be viewed as inequitable, and given a lack of remaining time or resources to provide translations for tools (including audio for the video) in 3 languages, the pilot study was launched with only English-language tool versions.

#### Intervention Conditions

##### Education-Only Arm

Participants received informational materials (including a fact sheet covering *frequently asked questions* [Multimedia Appendix 2] and a short video [Multimedia Appendix 3]) on their HIV treatment options and related support service options. These materials provide a comparison of the risks and benefits of LAI and oral ART regimens, set expectations about clinic visits, present information about side effects, and include additional resources to assist patients in preparing to discuss HIV treatment and support options with their care coordinator and prescribing provider. All materials are at or below an eighth-grade reading level, use graphics to bolster understanding for different levels of health literacy, and follow accessibility guidelines for font choice and size. Participants receiving this intervention were offered these materials by a care coordinator or patient navigator and were encouraged to review the materials on their own; they could also go over the materials with staff during an MCM program visit.

##### Decision-Aid Arm

Before or during an MCM visit, participants received informational materials (described in *Education-Only Arm* section) on HIV treatment types and related support service options. During an MCM visit, the participant and patient navigator or care coordinator reviewed the shared decision aid (Multimedia Appendix 4) to weigh the participant’s treatment options and their fit to the participant’s interests, needs, assets, and constraints. The tool facilitates and records patient-provider agreement on a treatment plan to be integrated into the broader MCM care plan signed by both the patient and provider. Figure 1 illustrates the 2 intervention conditions and the workflow for each.

**Figure 1 figure1:**
[figure not shown]
Intervention arms and workflows for the 2-arm pilot trial. eSHARE: Electronic System for HIV/AIDS Research and Evaluation.

##### Nonrandom Assignment

We used purposive sampling to assign 3 of the 6 partnering RWPA MCM agencies to the decision-aid arm (which included the educational tools) and 3 to the education-only arm. Specifically, we ensured representation of at least 2 different agency types and MCM program sizes in each arm.

##### Blinding

Owing to the need to engage service providers in the intervention through study team–led activities (eg, orientation to the project-specific educational materials or the decision aid), study arm assignments were transparent to agency staff and study team members (though not to patients).

#### Data Collection and Management

Aim 3 (pilot testing) involved repeated primary data collection with 2 providers at each of the 6 partnering agencies and use of secondary data on pilot participants, service delivery, and outcomes. In aim 3 pilot interviews with the implementing providers, oral informed consent was obtained in advance of the interview session by phone or videoconference. The interviews were audio-recorded and transcribed for coding in Dedoose. Aim 3 provider survey data were collected and managed using the NYC Health Department REDCap (Research Electronic Data Capture; Vanderbilt University) server, a web-based application for designing and managing surveys. The REDCap survey data will be analyzed using R (version 4.3.2; R Foundation for Statistical Computing).

Patient data for the pilot are being drawn from the local RWPA data system, the Electronic System for HIV/AIDS Research and Evaluation (eSHARE), in the form of provider-reported enrollments, services, patient characteristics, assessed needs, regimen types, and adherence data required for fee-for-service reimbursement in NY RWPA MCM contracts. eSHARE has been updated by the NYC Health Department to include pilot tools so that partnering MCM agencies could enter pilot activities along with (and as distinct from) other MCM services. No patients were enrolled in the RWPA MCM programs solely for the pilot; rather, patients already enrolled in MCM could be eligible to receive pilot-related services (ART regimen-related information and decision support with the tools developed for the project), along with the array of other MCM services. All patient- and service-level data are protected according to the Centers for Disease Control and Prevention’s physical and electronic data security and confidentiality policies [57]. Health Department staff extract and clean eSHARE data monthly, clean and freeze surveillance data sets quarterly, and conduct matches of the program to surveillance data semiannually. The deterministic matching algorithm has been described previously [58]. Through matching with surveillance data, patients are assigned a unique record number used to deduplicate data sets, which are stripped of personal identifiers before analysis.

#### Study Outcomes

##### LAI Uptake (Primary Outcome)

The primary outcome is defined as the proportion of pilot participants who start LAI ART (whether initiating ART, transitioning from a prior regimen, or transitioning from a period of nonuse of ART). The denominator includes patients not already on LAI ART at the start of the pilot trial, and the numerator includes any of those in the denominator who began LAI ART during the trial. Using program-reported (eSHARE) data on regimen type, uptake will be measured continuously for up to 9 months (the duration of the pilot trial). *Concordance:* This outcome is defined as the proportion of participants whose intent (as documented via the decision aid) is carried through in terms of their subsequent treatment (self-administered daily oral ART, LAI ART, or some intermediate step such as directly observed therapy to meet the current FDA label requirement for viral suppression). Using eSHARE data on decision aid responses and subsequent regimen type or services related to ART adherence, concordance will be measured from the date of decision aid completion for up to 9 months. *LAI maintenance:* LAI maintenance is defined in terms of adherence to LAI ART, specifically the time from LAI initiation to first deviation from the injection schedule, among trial participants initiating LAI ART during the trial. A deviation includes any injection >1 week ahead of or 1 week after the treatment target date, where the injection target date depends on whether the prescribed regimen is monthly or bimonthly. Using eSHARE data on ART regimen type and adherence (as well as case closure owing to death), maintenance will be measured from the first report of LAI ART to the first reported deviation from the injection schedule or date of death from any cause, whichever comes first, assessed for up to 9 months from the first injection or up to 8 months of follow-up injections (counting from the first possible deviation from a scheduled follow-up injection).

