3	Individual provider interviews	12 MCM providers (1 administrator and 1 direct-service provider per partnering agency)	Providers’ experience of the pilot, barriers and facilitators, or other factors for pilot tool implementation, and any recommendations	September 2023 to February 2024	Qualitatively assess pilot implementation factors and outcomes and desired changes to piloted tools
3	Program data on patients enrolled and pilot-related service delivery	≥180 MCM patients from 6 partnering agencies	Patient descriptive data, assessments of patient ART regimen and adherence, and detail on pilot services delivered (tools and dates used, as well as patient responses on ART regimen choices)	May 2023 to January 2024, with follow-up on LAI ART adherence through September 2024	Quantitatively assess pilot implementation outcomes such as reach, effectiveness, adoption, and implementation and variation by agency, intervention condition, or stage of pilot

^a^MCM: medical case management.

^b^LAI: long-acting injectable.

^c^ART: antiretroviral therapy.

The study functions as an academic-government-provider collaboration, with a university-based lead agency working closely with a health department and 6 NY RWPA MCM service-provider agencies that were engaged as partners from the outset. The 6 provider agencies were purposively selected to represent the full range of NY RWPA MCM service settings (hospitals, community health centers, and social services community-based organizations) and the distinct geographic regions within the NY RWPA eligible metropolitan area. Three of the agencies have headquarters in NYC, which includes 5 counties: New York (Manhattan), Bronx, Kings (Brooklyn), Queens, and Richmond (Staten Island). The other 3 agencies have headquarters in the Tri-County area north of NYC: Westchester, Rockland, and Putnam. All 6 agencies had an annual caseload of at least 70 RWPA MCM patients at the time of the study proposal development. Although the FDA had not approved LAI ART until after the study proposal was submitted, LAI ART prescription was beginning when the project started and was being considered for some MCM enrollees at the partner agencies by the second year of the project in the months immediately preceding the pilot.

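### LAI uptake and its arm comparison count only patients entered by staff who knew the arm, with no eligible-patient denominator to show whether selection differed between arms

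*Protocol article*

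**What the plan says.** Under LAI Uptake (Primary Outcome), the article says "The primary outcome is defined as the proportion of pilot participants who start LAI ART", and adds "The denominator includes patients not already on LAI ART at the start of the pilot trial". The section on sample size, data analysis and power analysis compares uptake between arms by a log binomial risk ratio, using generalized estimating equations with a small-sample correction. Adjustment for eSHARE confounders is planned as far as the sample size allows.

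On how patients come in, Data Collection and Management says "patients already enrolled in MCM could be eligible to receive pilot-related services". The data reach the study "in the form of provider-reported enrollments, services, patient characteristics, assessed needs, regimen types, and adherence data". Agencies were assigned purposively, three to each arm (Nonrandom Assignment), and under Blinding "study arm assignments were transparent to agency staff and study team members (though not to patients".

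On the pool, Study Overview, Aims, and Partners says "All 6 agencies had an annual caseload of at least 70 RWPA MCM patients", as counted when the proposal was developed. Pilot Trial Design describes reach by the types and numbers of patients enrolled. Table 1 adds that implementation outcomes, including reach, will be examined for variation by agency and intervention condition.

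**The concern.** Assignment was by agency and the arm was known to staff, so the set of patients entered at each agency is itself formed after assignment. If staff in one arm tended to bring in patients already leaning towards LAI ART, that arm would show higher uptake even if the decision aid did nothing. If they tended to bring in patients for whom LAI ART was unlikely, a real effect could be hidden.

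The article gives some reason to think likely starters could be recognised. Study Overview, Aims, and Partners says LAI ART was already under consideration for some MCM enrollees at partner agencies in the months just before the pilot. The uptake numerator counts any start during the trial by a patient in the denominator.

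The planned analysis does not separate selection from effect. The GEE correction deals with clustering. The eSHARE content listed does not include prior interest in LAI ART. The decision aid records patient intent, but only in one arm and after entry, so it cannot serve as a baseline covariate. Limitations and Strengths names non-random agency assignment and lack of blinding, but not selection of patients within agencies. Two results are at stake: the arm risk ratio, and the uptake proportion meant to inform sample size for a larger study.

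**Working it through.** **1. The plan's own figure.** Table 2 is a Wilson score interval with z = 1.96 and n = 180: centre (p + z²/2n)/(1 + z²/n), half-width z·√(p(1−p)/n + z²/4n²)/(1 + z²/n). At p = 0.10 the centre is 0.1107/1.0213 = 0.1084 and the half-width 0.0442, giving 6.4% to 15.2% (6.42 to 15.25 before rounding), as printed. All cells agree to about 0.1 point. Table 2 is sound, but it measures sampling error only and carries no allowance for who was entered.

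**2. Room for selection.**
- Caseload floor: 6 × 70 = 420 per year.
- Rough alternative, assuming the six agencies are of average size: 4000/29 × 6 ≈ 828, from the Introduction's count of more than 4000 patients in 29 programs.
- Target: 180/420 = 43%, or 180/828 = 22%.
- Mid-November 2023: 205/420 = 49%, or 205/828 = 25%.

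These are shares of an annual, proposal-stage caseload, not of eligible patients.

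**3. Effect of selection when the tool does nothing.** Assume both arms have the same true uptake p. One arm enters patients at random. The other enters eventual starters with odds OR times those of other patients. Let s1 and s0 be the entry probabilities of starters and non-starters, and f the entered fraction. Solve p·s1 + (1−p)·s0 = f with s1/(1−s1) = OR·s0/(1−s0). Observed uptake is then p·s1/f. The values of OR and p are assumptions; the article gives neither.

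Worked case with f = 180/420 = 0.429, p = 0.15, OR = 2: s1 = 0.574 and s0 = 0.403. Observed uptake is 0.15 × 0.574/0.429 = 20.1%, and RR = 20.1/15 = 1.34.

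Range of RR over p = 5% to 20%:

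| Caseload / entered | OR 1.5 | OR 2 | OR 3 |
|---|---|---|---|
| 420 / 180 | 1.19–1.22 | 1.32–1.38 | 1.50–1.59 |
| 420 / 205 | 1.17–1.20 | 1.28–1.33 | 1.43–1.50 |
| 828 / 180 | 1.27–1.33 | 1.48–1.60 | 1.79–2.01 |

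**4. The other direction.** With caseload 420, 180 entered and OR 2 acting in opposite directions in the two arms, RR is 1.89 to 2.12. At p = 15% it is 1.96, so the arm selected away from starters would show 1.34/1.96 = 0.68 relative to random entry.

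**5. A second model.** Suppose 20% of the caseload is inclined to LAI ART with 40% uptake, and the rest has 3%. True uptake is 0.2 × 0.40 + 0.8 × 0.03 = 10.4%. If one arm is twice as likely to enter inclined patients, their share is 0.4/1.2 = 33.3%, uptake is 15.3% and RR 1.47. At 1.5 times, the share is 0.3/1.1 = 27.3%, uptake 13.1% and RR 1.26. With 50% inclined, true uptake is 21.5% and the two RRs fall to 27.7/21.5 = 1.29 and 25.2/21.5 = 1.17.

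**6. Whole-caseload denominator.** In these no-effect scenarios RR is 1.00 by construction, because entry no longer decides who is counted. The price is dilution. With equal baseline uptake and no spillover, a true RR of 1.5 among recipients becomes 1 + 0.5 × 0.25 = 1.13 at 25% reach and 1 + 0.5 × 0.49 = 1.25 at 49%.

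**The case against.** The strongest reply is that this is a pilot sized for precision on overall uptake. Arm effects are called preliminary, a larger controlled study is to follow, and the purposive 3 v 3 assignment is already disclosed. A journal article may also leave the approach rule to the full protocol. All of this stands, and it limits how much weight the point can carry. It does not remove it, because the article still sets out an arm comparison of the fuller package against education alone and plans to use the uptake estimates for sizing.

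Several stronger readings are tempting and are not supported:

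- **That entry differs by arm.** The workflows do differ: "During an MCM visit, the participant and patient navigator or care coordinator reviewed the shared decision aid", while education-only patients were encouraged to review materials on their own. But the article does not define the event that makes someone a participant, both arms receive the same materials, and the workflow figure is not shown. Entry could differ; it is not shown to.
- **That staff hand-picked patients.** No passage says so. What can be said is that staff knew the arm and no approach rule is stated.
- **That 25% to 49% is the reach among eligible patients.** Seventy is a proposal-stage annual caseload. Exclusion of known or suspected resistance, the English-only launch and current LAI ART use all reduce it, and 205 is an interim count. True coverage could be materially higher.
- **That the decision-aid arm is favoured.** The direction is unknown. The article also reports that virally unsuppressed patients were harder to engage in research, so selection could run either way.

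The planned breakdown of implementation outcomes by agency and condition, and the tracking of tool use, are real partial safeguards. They describe those enrolled and still lack an eligible denominator.

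**Conclusion.** The point holds as a moderate one. The uptake denominator and the arm risk ratio rest on patients entered after agency assignment at sites where the arm was known. Nothing described in the article would let a reader tell an effect of the decision aid from a difference in who was entered. Moderate selection in one arm would give an RR of about 1.2 to 1.6 with no tool effect (caseload 420, 180 entered, OR 1.5 to 3, true uptake 5% to 20%). A lower inclination contrast or higher coverage would give less; a larger caseload or opposing selection would give more. These are illustrations of what is possible, not estimates of bias in this trial. A reader might infer that the enrolled-patient comparison is invalid and should be replaced. The documents do not support that: replacement would change the question asked and dilute any true effect. The case is for reporting a second comparison beside it.

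**What to change.** Keep the enrolled-patient uptake proportion and arm comparison as planned, and add:

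1. **Reach with a denominator.** Report enrolled divided by eligible MCM patients not already on LAI ART, by agency and arm. Tabulate the eSHARE characteristics of enrolled and not-enrolled eligible patients.
2. **A co-reported sensitivity comparison.** Report LAI ART uptake among all such patients open in MCM at the six agencies during the pilot, whether or not they received the tools, counted in their agency's arm.

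Neither addition changes conduct. Regimen type and adherence are reported to eSHARE for MCM reimbursement, so the data should largely exist beyond pilot participants; completeness needs checking. The costs are a wider extract, some further analysis and possibly an IRB modification, since it is not stated that the consent waiver covers non-participants.

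Limits to state with the results: the caseload comparison is diluted by incomplete reach, resistance status may not be recorded for patients not enrolled, and confounding from purposive assignment of six agencies remains in both comparisons.

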**Results:**

The study was funded in late April 2021 and received approval from the institutional review board in May 2021 under protocol 20-096. Focus groups were conducted in late 2021 (n=21), DCEs ran from June 2022 to January 2023 (n=378), and tools for piloting were developed by May 2023. The trial (May 2023 through January 2024) has enrolled >200 patients.

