##### Sample Size, Data Analysis, and Power Analysis

The original target was to enroll 180 patients or 30 (on average) per partner agency. As of mid-November 2023, 205 patients were enrolled. Using eSHARE data, we will describe trial participant demographics (eg, gender, age, race or ethnicity, income, and housing status) overall and by intervention arm. We will compare LAI ART uptake and, among those starting LAI ART, adherence by intervention arm, to assess the effects of the fuller package with the decision aid versus education alone. We will use log binomial regression to estimate risk ratios for uptake and adherence by intervention arm with generalized estimating equations and a small sample correction (owing to the small number of clusters) to maintain the type I error rate while accounting for clustering by site. To the extent possible given our sample size, we will adjust for potential confounders captured in eSHARE.

The brief provider survey measures will be analyzed through a comparison of responses on the same measures over time (eg, to assess change in perceived feasibility), as well as comparison of responses by intervention arm, agency type, and participant role. AIM, IAM, FIM, and ORIC scores will also be analyzed in relation to the levels of pilot service delivery as documented in eSHARE. To understand the potential for sustainability and scale-up, we will explore qualitative provider interview themes related to the acceptability and feasibility of the intervention. Qualitative and quantitative analyses will be integrated by examining thematic patterns reflecting RE-AIM and CFIR implementation constructs as they explain observed implementation outcomes [61].

Our pilot was designed to assess implementation of the newly developed tools and inform tool refinements. Data from the pilot will be used to generate estimates of LAI ART uptake that can, in turn, inform sample size and power calculations for a larger, controlled study of the refined tools’ implementation and treatment outcomes. Accordingly, data from the pilot study will be used to estimate the proportion of patients who start LAI ART and, among those initiating, the proportion who maintain LAI ART. With the original target of 180 patients (now exceeded), we will be able to estimate LAI uptake with precision (95% CI) with the levels of uptake described in Table 2.

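### The primary outcome fixes LAI status at trial opening rather than at each patient's enrolment, so LAI starts before any contact with the tools can count as uptake

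*Protocol article*

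**What the plan says.** The Protocol article, under LAI Uptake (Primary Outcome), sets the denominator as follows: "The denominator includes patients not already on LAI ART at the start of the pilot trial". For the numerator, "the numerator includes any of those in the denominator who began LAI ART during the trial". The observation window is tied to the trial calendar: "uptake will be measured continuously for up to 9 months (the duration of the pilot trial".

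The two other outcomes in that section each have a patient-level time zero. For the first, "concordance will be measured from the date of decision aid completion for up to 9 months". Maintenance runs from the first report of LAI ART, among participants who initiate it during the trial.

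On timing, the abstract's Results state: "The trial (May 2023 through January 2024) has enrolled >200 patients". The sample size section adds: "As of mid-November 2023, 205 patients were enrolled". On the source of participants, Data Collection and Management says that "patients already enrolled in MCM could be eligible to receive pilot-related services". Study Setting and Participants lists program enrolment, age and language, and asks programs to leave out patients with known or suspected resistance to the LAI drugs. It does not exclude a patient who is on LAI ART when enrolled.

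LAI prescribing had begun before the pilot. Study Overview, Aims, and Partners says that LAI ART "was being considered for some MCM enrollees at the partner agencies by the second year of the project".

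**The concern.** Nothing in the definition requires an LAI start to come after enrolment, or after the fact sheet, video or decision aid was received. Take a patient who is on oral ART in May 2023, starts LAI ART in July and is first given a pilot tool in October. That patient is in the denominator and counts as a success, although the tools cannot have influenced the start.

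Three uses of the data are affected:
- The overall uptake proportion, which the article intends to use for sample size planning of a larger study, is too high.
- The risk ratio between the decision-aid and education-only arms mixes starts that the tools could have influenced with starts that they could not.
- The maintenance cohort, made up of those initiating during the trial, takes in the same pre-enrolment starters.

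**Working it through.** **Plan's own figure.** Table 2 is the only numerical planning for this outcome. It is reproduced by the Wilson score interval with n = 180: centre (p + z²/2n)/(1 + z²/n), half-width z·√(p(1−p)/n + z²/4n²)/(1 + z²/n). At p = 0.10 the centre is 0.1084 and the half-width 0.0442, giving 6.4 to 15.3 against 6.4 to 15.2 in the table. The other uptake rows also agree within 0.1 point. The table is sound, and the concern does not depend on it.

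**Does the definition let the case in?**
1. The anchor for LAI status is the start of the pilot trial. The window is equated with the trial's duration, and May 2023 through January 2024 is nine months.
2. Enrolment was by patient and cumulative: 205 by mid-November 2023, about 6.5 months after an opening at the start of May.
3. Participants came from existing caseloads, so their regimen records can predate the pilot tools.
4. Current LAI use is not an exclusion.

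A start between opening and enrolment therefore meets both the denominator and the numerator rule.

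**Crude start rates from the article.**
- National (Introduction): 20,000 / 1,100,000 = 1.82% on the product at the end of September 2023, about 32 months after approval in January 2021. 1.82 / 32 = 0.057% per month.
- These agencies (patient survey): 9/201 = 4.48% had tried LAI ART, surveyed June 2022 to January 2023, about 17 to 24 months after approval. 4.48 / 24 = 0.19% and 4.48 / 17 = 0.26% per month.

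**Mean wait before enrolment (assumption).** Uniform enrolment over 6.5 to 9 months gives a mean of 3.25 to 4.5 months. The article gives no enrolment curve.

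**Share of participants who are pre-enrolment starters:** 1 − exp(−rate × wait), assuming that they are enrolled as readily as others.

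| Rate per month | Wait (months) | Share |
|---|---|---|
| 0.057% | 3.25 | 0.2% |
| 0.19% | 3.25 | 0.6% |
| 0.26% | 4.5 | 1.2% |

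Of 180 patients, 0.2% to 1.2% is about 0 to 2.

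**Effect on uptake.** With pre-enrolment share s and true post-enrolment uptake 10%, recorded uptake is s + (1 − s) × 0.10, so the increment is 0.9s. This is 0.9 × 0.2 to 0.9 × 1.2, or roughly 0.2 to 1 percentage point.

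**Effect on the arm risk ratio** (illustrative uptake values).
- Equal shares, true 20% vs 10% (RR 2.0). At s = 1%: (0.01 + 0.99 × 0.20)/(0.01 + 0.99 × 0.10) = 0.208/0.109 = 1.91. At s = 2%: 0.216/0.118 = 1.83.
- Unequal shares, no true effect (10% in both arms). At 1.2% vs 0.2%: (0.012 + 0.0988)/(0.002 + 0.0998) = 0.1108/0.1018 = 1.09; reversed, 0.92. A larger imbalance of 6% vs 2%, well above what the article's rates suggest, gives 0.154/0.118 = 1.31; reversed, 0.77.

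**The case against.** The strongest reply is that the text can be read with a patient-level clock. The outcome concerns pilot participants, and a window of up to nine months also fits a count from each patient's entry, with the bracketed phrase giving only the maximum. An unseen analysis plan may set an index date. This reading strains the wording: the denominator clause names the start of the trial, while concordance and maintenance in the same section have explicit patient-level anchors. The article states a rule here; it does not leave one open.

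The objections on size carry more weight. A reader might infer that several points of recorded uptake predate the tools. At 1% per month and a 4.5-month wait, 1 − exp(−0.045) = 4.4%. The documents do not support that rate: it is about four times the upper average at these agencies (1/0.26 = 3.8). Staff also have little reason to offer a regimen-choice tool to someone who has just started LAI ART, and enrolment may have been front-loaded. On the other side, start rates may have risen by 2023, so the crude averages are not an upper bound.

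A reader might also infer that the arm comparison is biased in favour of the decision aid. The article gives no enrolment timing or pre-enrolment starts by agency, so it shows no direction. Equal starts dilute the contrast.

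Finally, this is a pilot seeking preliminary effects. That limits the consequences but does not make the definition right.

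**Conclusion.** The point holds as a defect in the stated definition of the primary outcome. LAI starts between trial opening and a participant's enrolment or first tool use count as uptake, although they cannot result from the tools. The actual number is unknown. On the article's crude rates and the assumed wait it is about 0.2% to 1.2% of participants, adding roughly 0.2 to 1 point to a true 10%. That is small beside the Table 2 interval of 6.4 to 15.2. It would be more if start rates had risen by 2023, and less if recent starters were seldom given the tools. The risk ratio moves towards 1 if pre-exposure starts are equal. With six purposively assigned agencies, it could move either way if they are not.

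It would go too far to say that all usual-care uptake is credited to the tools because of this anchor. Both arms receive educational materials, so background starts after enrolment count under any anchor. The correction removes only the starts that come before exposure.

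**What to change.** Define the denominator as participants not on LAI ART at their own pilot enrolment, taken as the first documented pilot-tool date in eSHARE. Count only LAI starts after that date. Apply the same rule to the maintenance cohort. Report LAI starts between trial opening and enrolment separately, by agency, so that any imbalance between arms can be seen.

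The change is short and needs no new source: Table 1 lists tools and dates of use among the program data, and eSHARE holds regimen type. It has two costs. The denominator becomes slightly smaller. Regimen data are provider-reported, so a first report after the tool date may reflect an earlier start; LAI start dates need checking where reports lag.
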